### Blinding

Assessors will be blinded about children’s allocation group. In this sense, the draw for children randomization will be carried out by a professional not involved in the assessments and interventions of the project. Blind statistical analyses will be performed, having children’s names and intervention groups modified by numeric codes in the spreadsheets.

### Statistical methods

At first, descriptive analysis will be done with the distribution of relative and absolute frequencies, averages, standard deviations, medians, mode, and minimum and maximum number in order to characterize children. All data will be inserted into spreadsheets in the SPSS statistical package, version 20.0 for Windows.

Next, analyses regarding normality and homogeneity tests will be performed. There will be two independent groups because of the design of the study, and there will also be intergroup comparative analyses in each one, constituting the results of motor performance and learning evaluation pre test and post test, as well as the comparisons between such intergroup evaluations.

In case of parametric distribution, analyses will be performed through analysis of variance (ANOVA) and analysis of co-variance (ANCOVA) utilizing the Bonferroni correction.

In case of non-parametric distribution, intergroup comparative analyses will be carried out by means of the Mann-Whitney *U* test and intergroup comparison through the Wilcoxon test. The significance level adopted will be *p* < 0.05 for all measurements. In order to verify the dimension of the effect of the interventions realized, the Cohen test will be applied with the following reference values: *d* = 0.3 indicates a small dimension of the effect, while *d* = 0.5 and *d* = 0.8 indicate a moderate and a large one [30], respectively.

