More specifically, the use of the Nintendo® Wii in the rehabilitation of children with motor alterations has been promoted for ease of measuring the force applied and capturing pressure change available in the Wii Balance Board (WBB), besides the fact that the Wii motion control allows great stimulation of the hand-dexterity motor component [15, 16]. Balance, Aiming and Catching are the domains of the Movement Assessment Battery for Children (MABC), that are regarded as the gold standard for the identification of DCD in children [17]. These aspects make the Nintendo® Wii very useful as a VR resource for motor interventions in children with DCD.

At present, however, little evidence exists in the literature on comparisons between the benefits of VR training, such as Nintendo® Wii, and conventional interventions such as without Wii [18–20].

The handful of existing studies that compare interventions with and without VR for children with DCD still show limitations about evidence created by the VR intervention [19, 21–24]. Moreover, it is not clear whether one type of intervention offers greater gains than the other due to the shortcomings from the scarce previous studies already published. Based on a recent systematic review by Hickman et al. [25] evidence for advantages gained by a VR intervention for children with DCD are not consistent in relation to conventional therapy. The authors argued that due the heterogeneity of assessment tools and outcomes fair comparisons were not possible. So, we believe that in this study we might see fair comparisons because the tasks will be closely matched by motor domain target into the training protocol.

These limitations of present approaches hinder a well-informed conclusion as to whether training with VR is more effective than conventional training in children with DCD. In this paper we present a protocol for a randomized clinical trial to systematically compare two motor-training programs (with and without Nintendo® Wii) on motor learning in children with DCD.

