Criteria D – The motor limitations showed by the children do not come from intellectual or visual impairment, or neurologic conditions such as cerebral palsy, dystrophy or any degenerative disease. In order to eliminate these associated conditions, school data about the children will be assessed, teachers will be interviewed and also physiotherapists will offer assessments in order to eliminate any sign of the mentioned neurologic conditions. In addition, psychiatric disorder history will be assessed through the parents’ interview as well as based on children’s forms at school in order to avoid the heterogeneous profile of those children. If we find children who have already received a psychiatric diagnosis (other than DCD) we will exclude them from the study. In addition, we will exclude children who may have undiagnosed psychiatric conditions but have recognizable contra-indications such as high levels of anxiety, impulsivity or attentional difficulties.

Highly anxious, inattentive or oppositional children who might be unable to complete either intervention program will be excluded from the study because they might find the interventions distressing. Children will be allowed to continue regular physical education classes at schools. Other concomitant care or interventions during the period of intervention will not be allowed.

In case any children are missed before the intervention ends, we use the intention-to-treat analysis.

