### Primary outcome measure

#### The primary outcomes of this study is the motor performance

##### Motor performance – MABC-2

The motor performance of the children will be assessed through the MABC-2 total standard score (TSS). As mentioned before, MABC-2 is considered a gold standard tool to identify motor performance problems in children from 3 years old. MABC-2 is divided in three different age bands: the band 1 for children aged from 3 to 6 years old; band 2 for children aged from 7 to 10 years old; and band 3 for children aged from 11 to 16 years old. There are eight tasks in total, three for the Manual Dexterity domain, two for the Aiming and Catching domain; and three for the Balance domain. Children received a specific score in each domain and their motor performance classification is based on total score and percentiles values. Children < 5° percentile present motor difficult; children < 16° percentile are at risk for motor difficult and children > 16° percentile have no motor difficult detected. According to the MABC-2 tester manual, each child spends about 30–40 min completing all tasks.

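### A normality test picks the method, no single between-arm test of MABC-2 is named as primary, and the within-arm Wilcoxon carries a between-arm label

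*Protocol article*

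**What the plan says.** Under Statistical methods, the protocol article describes the data and then states: "Next, analyses regarding normality and homogeneity tests will be performed". The result decides the route.

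- Parametric route: "In case of parametric distribution, analyses will be performed through analysis of variance (ANOVA) and analysis of co-variance (ANCOVA) utilizing the Bonferroni correction". The section does not say which of the two models answers the trial's question, or what the covariate is.
- Non-parametric route: "In case of non-parametric distribution, intergroup comparative analyses will be carried out by means of the Mann-Whitney" U test, followed by "intergroup comparison through the Wilcoxon test". Whether Mann-Whitney takes post-test or change scores is not stated.

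Of the two independent groups the section says "there will also be intergroup comparative analyses in each one", so the analyses inside each group also carry the between-group label. The same sentence goes on to promise comparisons of those evaluations between groups. Bonferroni appears only in the parametric route, while a 0.05 level is set for all measurements.

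Elsewhere, the Background sets a between-arm aim (training with Wii against training without), the primary outcome section names the MABC-2 total standard score, and the Abstract has MABC-2 applied before and after the intervention. Sample size rests on the pre-to-post change within the Wii group.

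**The concern.** The trial asks whether one programme does better than the other. The plan leaves open which test answers that, and lets a preliminary test on about 16 children per arm choose the route. Two consequences follow.

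First, with both the Wilcoxon and the analyses inside each group labelled as between-group, a report could follow the published text and present a significant change in one arm, without one in the other, as a difference between arms. It is not evidence of one. The within-group basis of the sample size makes this risk more than theoretical.

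Second, Mann-Whitney takes no covariate. If the gate fails, the trial loses adjustment for the baseline MABC-2 score, which it collects anyway and which is likely to be its most useful covariate. The multiplicity rule also changes with the route, so error control on the secondary outcomes depends on the normality result.

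**Working it through.** **Inputs from the protocol article (Sample size).** Within-group comparison in the Wii group, effect size 0.80, power 80%, alpha 5%, 15 per group, raised to 16 (read here as per arm).

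**Assumptions, because the article gives no figure.** Between-arm standardised difference d = 0.8; correlation r between baseline and post-test of 0.5 to 0.7; two-sided 0.05; equal SDs.

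**1. The plan's own figure.** Two-sided paired t-test, noncentrality dz√n = 0.80 × √15 = 3.10 on 14 df: power 82.1%. With n = 14 it is 79.0%. So 15 reproduces as a within-arm test. An independent-groups t-test at d = 0.80 would need 26 per arm (80.7%).

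**2. Separate within-arm tests when the arms do not differ.** Both arms have the same true gain, and each is tested alone with power p. The chance that exactly one is significant is 2p(1 − p).
- dz = 0.8, n = 15: 2 × 0.821 × 0.179 = 0.29. Simulation with the Wilcoxon gave 29.9%.
- dz = 0.5, n = 15: 2 × 0.438 × 0.562 = 0.49.

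A between-arm test has a 5% error rate in the same situation.

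**3. Power of each between-arm test at 16 per arm, d = 0.8, normal data.**
- ANCOVA on baseline: effective d = 0.8/√(1 − r²), noncentrality effective d × √8, 29 df.
- Mann-Whitney: t-test approximation with effective n = 16 × 3/π = 15.3 per arm. For change scores, effective d = 0.8/√(2(1 − r)).

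| r | ANCOVA | Mann-Whitney, post | Mann-Whitney, change |
|---|---|---|---|
| 0.5 | 71% | 57% | 57% |
| 0.6 | 78% | 57% | 67% |
| 0.7 | 86% | 57% | 79% |

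**4. Effect of the gate on the whole procedure.** Simulation, 3,000 runs per setting (standard error up to about 0.9 points): Shapiro-Wilk on each arm's post scores, ANCOVA if both pass, Mann-Whitney on post scores otherwise.

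| Data | r | Sent to fallback | Two-stage power | ANCOVA always | Rank ANCOVA always |
|---|---|---|---|---|---|
| Normal | 0.5 | 10% | 68.0% | 68.9% | 65.6% |
| Normal | 0.7 | 9% | 83.0% | 85.3% | 81.3% |
| Moderate skew | 0.5 | 41% | 68.1% | 70.0% | 72.3% |
| Moderate skew | 0.7 | 40% | 77.5% | 85.1% | 87.1% |
| Heavy tails | 0.5 | 36% | 74.1% | 72.3% | 79.9% |
| Heavy tails | 0.7 | 35% | 83.2% | 87.1% | 91.6% |

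A second simulation with normal data gave 70% against 71% (r = 0.5) and 82% against 85% (r = 0.7). With no true difference, the two-stage procedure rejected in 5.0% to 6.1% of runs, so its type I error is close to nominal.

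**The case against.** The strongest reply is that each route already contains a valid between-arm test: ANOVA/ANCOVA in one, Mann-Whitney in the other. The section also promises to compare the evaluations between groups. The label on the Wilcoxon is then a slip for intragroup, and nobody is told to draw the conclusion from within-arm results. That stands. A reader might infer that the plan is built to yield a within-arm conclusion; the text only leaves room for one.

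A reader might also take the gap in the fallback (up to 29 points at r = 0.7) as the plan's power loss. The article does not support that. The gap applies only when normality is rejected, and only if Mann-Whitney is run on post scores. On change scores at r = 0.7 it is about 7 points. With heavy tails and r = 0.5 the gate did slightly better than ANCOVA always (74.1% against 72.3%), although rank ANCOVA beat both.

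Two further inferences should not be drawn.
- Ten motor-learning comparisons at 0.05 would give 1 − 0.95^10 = 40% false positives only if independent. The domain and total scores are sums of the same six games, so they cannot be.
- The listed tests do not by themselves contradict the promise under Patient population ("In case any children are missed before the intervention ends, we use the intention-to-treat analysis"). The article does not say how missing post-tests are handled, and that may be set out in an analysis plan not shown.

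The unnamed covariate could also be settled there. That does not remove the point: the article itself states the decision rule, and the rule is what needs changing.

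**Conclusion.** The point holds as a should-fix. The protocol article lets a preliminary test choose the primary method, names no single between-arm analysis of the MABC-2 total standard score, and labels within-arm tests as between-arm. The more serious consequence is interpretive: if the conclusion were drawn from separate within-arm p-values, arms with equal gains would look different in about 29% of trials at dz 0.8, or 49% at dz 0.5. The text allows that use but does not prescribe it.

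The efficiency cost is modest overall: about 1 to 3 points of power with normal data, and 7 to 8 with moderate skew at r = 0.7. These figures rest on an assumed between-arm d of 0.8, an assumed correlation, a Shapiro-Wilk gate on post scores, and Mann-Whitney on post scores. The between-arm tests themselves are valid. Whether 16 per arm is enough is a separate question.

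**What to change.** Replace the two-route rule for the primary outcome with one analysis: ANCOVA of the post-test MABC-2 total standard score on arm, with baseline MABC-2 as covariate, two-sided 0.05, whatever the normality tests show. Report the adjusted difference with its 95% confidence interval.

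Add a baseline-adjusted rank or permutation test as a sensitivity analysis. Relabel the Wilcoxon and any other paired tests as within-arm and descriptive, and state that they are not a basis for the Wii versus no-Wii conclusion. Apply one multiplicity rule to the secondary outcomes regardless of their distribution.

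The cost is wording and slightly more analysis work. No extra children or measurements are needed, since MABC-2 is already taken before and after. The downside is reliance on the ANCOVA model in a small sample, which the sensitivity analysis covers.

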### Secondary outcomes measures

#### Motor learning

Motor learning in children will be assessed by means of the score obtained in the games. Individual scores in each of the six games from the second session (pre-test) will be summated as well as those from the six games of the last session (post-test) to obtain the general measurement of motor learning due to the treatment.

Individual scores in each game and for domain will also be counted (Manual Dexterity, Aiming and Catching, and Balance), before and after intervention. With the purpose of analyzing whether some activities are better learned in one type of intervention than in another. A specific form will be available for each therapist fills this information in each session.

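### Game- and domain-level motor-learning tests use p < 0.05 with no correction named on the rank-based route and a Bonferroni of unstated scope on the parametric route

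*Protocol article*

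**What the plan says.** The protocol article ranks its outcomes. Under Primary outcome measure it states "The primary outcomes of this study is the motor performance", measured by the MABC-2 total standard score. Motor learning stands under the secondary outcomes.

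Motor learning is scored at three levels:
- **Total.** "Individual scores in each of the six games from the second session (pre-test) will be summated", and likewise for the last session, as a general measure of learning.
- **Games and domains.** "Individual scores in each game and for domain will also be counted (Manual Dexterity, Aiming and Catching, and Balance), before and after intervention".
- **Reason given for the game and domain scores.** "With the purpose of analyzing whether some activities are better learned in one type of intervention than in another".

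Statistical methods then gives two routes, chosen after normality and homogeneity tests. The parametric route is "analysis of variance (ANOVA) and analysis of co-variance (ANCOVA) utilizing the Bonferroni correction". On the other route, "intergroup comparative analyses will be carried out by means of the Mann-Whitney *U* test and intergroup comparison through the Wilcoxon test". One threshold closes both: "The significance level adopted will be *p* < 0.05 for all measurements".

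**The concern.** Looking across several activities for any that differ between arms is a multiple-testing question. A threshold of 0.05 on each test does not hold the overall error at 5%. The section applies that threshold to every measurement, and the one correction it names belongs to one of the two routes.

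Two things follow. First, on the rank-based route, followed as written, every game and domain is tested at 0.05 uncorrected. Second, on the parametric route the reader cannot tell whether Bonferroni runs across the outcomes or only across contrasts within one model. With two arms there is a single between-arm contrast per outcome, so a within-model correction would leave the set of outcomes uncorrected. The same scores could thus be held to different standards because of a preliminary test of distribution.

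At stake is the credibility of any statement that a particular activity is better learned with or without the Wii. Motor learning is a secondary outcome, but it is also what the Abstract and Background say the two programmes are compared on.

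**Working it through.** **The plan's own figures.** The article gives no overall error rate for these tests, so there is none to reproduce. The group size used below comes from Sample size. A paired t-test with effect size 0.80, 80% power and two-sided 5% gives n = 15 (power 82.1%), matching the article's 15 per group. The article raises this to 16, and 16 per arm is used here.

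**Count of scores.** 1 total + 3 domains + 6 games = 10. They are nested: each domain is the sum of two games, and the total is the sum of all six.

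**Reference for independent tests.** The chance of at least one false positive in k tests is 1 − (1 − 0.05)^k.
- Six games: 1 − 0.95^6 = 26.5%.
- Ten tests: 1 − 0.95^10 = 40.1%. This is too high here, because the ten scores overlap.

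**Simulation of the nested scores.** Assumptions: no true arm difference, 16 per arm, two-sided tests (the article does not state sidedness), normal scores, six games of equal variance with common correlation r, and 40,000 trials per setting. The article gives no value for r, so it is varied. Entries are the chance of at least one false positive.

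| r | Ten scores at 0.05, t-test | Ten scores at 0.05, Mann-Whitney | Six games at 0.05, t-test | Ten scores, Bonferroni (0.005 each), t-test | Six games, Holm, t-test | Six games, Holm, Mann-Whitney |
|---|---|---|---|---|---|---|
| 0 | 32.0% | 31.1% | 26.4% | 4.2% | 5.1% | 4.5% |
| 0.3 | 26.6% | 26.2% | 24.1% | 3.5% | 4.5% | 4.1% |
| 0.5 | 22.1% | 21.8% | 21.0% | 2.9% | 4.2% | 3.8% |
| 0.8 | 14.5% | 14.3% | 14.3% | 2.0% | 3.0% | 2.8% |
| 0.9 | 11.1% | 11.3% | 11.1% | 1.4% | 2.2% | 2.1% |

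With no true difference in any game, Holm makes a false claim only if its first step, at 0.05/6 = 0.0083, rejects. For six independent tests that is 1 − (1 − 0.05/6)^6 = 4.9%. The simulated 5.1% at r = 0 differs from this only by simulation error.

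**Sensitivity.** If one game dominates the sums of raw points, the ten-score rate is 30%, 26%, 22% and 17% at r = 0, 0.3, 0.5 and 0.7. The conclusion does not depend on equal variances.

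**Reading the table.** Uncorrected, the rate is at least twice 5% in every setting, whichever test is used. A Bonferroni correction that did cover all ten scores would hold it below 5%: 1 − 0.995^10 = 4.9% at most for independent tests.

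**The case against.** The other side has several good points.

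- **A correction is named.** A reader might infer that the plan leaves all ten comparisons uncorrected. The text does not support that for the parametric route, where Bonferroni is named and may cover the outcomes. The uncorrected reading is clear only on the rank-based route, and no distribution of game scores is given that would show which route will apply.
- **There is a ranking.** A reader might infer that the plan has no hierarchy, or that the main result is compromised. Neither holds. MABC-2 is primary, motor learning is secondary, and the primary test is outside this family. How secondary breakdowns are handled is often left to an analysis plan, which is not shown.
- **The total has its own purpose.** It measures learning overall and cannot show which activity is better learned. This stands but changes little: the six games alone give 21.0% at r = 0.5, against 22.1% for all ten scores.
- **Other outcomes.** A reader might count Enjoyment Scale items as further tests. The article collects that scale once and states no between-arm test of its items, so they are not counted. The Discussion's statement about the benefits of one programme over the other is made at programme level, not for single games.
- **Correction alone does not make the claim sound.** Paired activities are scored differently in the two arms. Marble balance gives one point per ball, while the balance disk gives 10 per posture. Tightrope sections are worth 15, 20 and 10, while the beams are worth 10, 15 and 20. A difference in raw points may reflect scoring alone. This stands, and it bears on the choice of fix.

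What remains is more than omitted detail. The article states a threshold for all measurements, states an inferential purpose for the game and domain scores, and ties its only correction to one of two routes.

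**Conclusion.** The concern holds in a limited form. The plan does not say what Bonferroni covers on the parametric route and names no correction on the rank-based route, so control of false claims about individual activities depends on a normality check.

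If the ten scores are tested uncorrected, the chance of at least one false claim is about 22% at a between-game correlation of 0.5, and about 11% to 32% for correlations from 0.9 to 0. These figures assume no true arm difference, two-sided tests and 16 children per arm. The correlation is not in the documents, so 22% is an illustration and the range is the result. The finding concerns secondary claims only and merits correction before the analysis.

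**What to change.** In Statistical methods, replace the single threshold for all measurements with a short ordered rule:

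1. The between-arm comparison of the MABC-2 total standard score is the only confirmatory test, at two-sided 0.05.
2. Domain and single-game motor-learning comparisons are exploratory, reported as estimates with confidence intervals, without claims of significance.
3. Alternatively, if a claim that an activity is better learned in one arm is wanted, test the six games with Holm at 0.05, identically on the parametric and the rank-based route. The family-wise rate is then about 2% to 5% over the correlations examined.
4. State which comparisons Bonferroni covers wherever it is kept.

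Option 2 is preferable to option 3, because Holm does not make raw points comparable where the two arms score paired activities differently.

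The cost is wording only, with no extra children, visits or measurements. The downside under Holm is that single-game p-values between about 0.008 and 0.05 may no longer count as significant.
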